**Methods:**

We describe a randomized controlled effectiveness trial in the frontline services of child welfare, health, school health and school psychological counselling services in 24 Norwegian municipalities. It is a two-armed parallel group randomized controlled effectiveness and superiority trial with 252 families randomly allocated to SPARCK or UC. Assessment of key variables will be conducted at pre-, post-, and six-month follow-up.

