### Aims and research questions

We will conduct a randomized controlled trial to investigate the effectiveness of SPARCK compared to usual care (UC) in Norwegian frontline services. In Norway, frontline municipal service sectors, such as child welfare, health, school health and school psychological counselling services, are responsible for providing targeted preventive interventions. The primary objective is to examine whether SPARCK is effective in preventing and reducing negative outcomes and promoting positive outcomes for children and parents. It has been pointed out recently [58], that studies on prevention of anxiety should assess actual disorders in a long-term perspective, and we answer this call by including register data on referrals to specialized services and/or contact with child welfare services. We will also conduct a parallel implementation study to examine the relationship between implementation determinants and clinical and implementation outcomes. However, in this study protocol we focus on the effectiveness part of the project. A separate implementation protocol will be written.

Considering the variability in the quality and quantity of the mental health services for children, youths, and families in the frontline services across Norway, in combination with the theoretical and empirical background presented above, our aim has been to develop a flexible and tailored intervention to address heightened, yet subclinical, symptoms of anxiety, depression, and/or externalizing problems among children and youths. Building on our understanding of the significance of engaging with parents, we posit that alterations in child symptoms will, in part, hinge on corresponding changes in parenting practices. We assume that enhancing parenting practices aimed at fostering children's proficiency in essential life skills could exert a positive influence on both healthy child development and parental well-being (see Fig. 2). Consequently, such interventions may serve as a preventive measure against more severe or enduring mental health problems.

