We posit several hypotheses to guide the investigation of SPARCK. More specifically, our primary hypothesis is: H1: Children of parents receiving SPARCK will exhibit lower levels of internalizing and/or externalizing symptoms compared to those who receive UC at a) the end of the intervention and b) 6 months post-intervention. Our secondary hypotheses are: H2: Parents in the SPARCK condition will demonstrate better parenting practices, self-efficacy, and less parental stress than parents in the UC condition at a) the end of intervention and b) 6 months post-intervention; and H3: The effect of SPARCK on child symptoms is mediated by changes in parenting practices; H4: Children (≥ 7 years) and parents in the SPARCK condition will report better subjective quality of life than children (≥ 7 years) and parents in the UC condition; H5: Among those who display abnormal blunted or elevated stress hormone levels as indicated by cortisol and DHEA at pre-intervention, children and parents in SPARCK will be more likely to change towards normative levels at post-intervention than those who receive UC; H6: Children in the SPARCK condition will display lower levels of school refusal than children in the UC condition at a) the end of intervention and b) 6 months post-interventions; and H7: Children in the SPARCK condition will be less likely to be referred to child and adolescent outpatient clinics (Norwegian abbreviation: BUP) or have contact with the Child Welfare Services (CWS) in the following two years compared to children in the UC condition.

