### Participants, recruitment, and randomization

The target group in this study is caretakers of children between 4 and 12 years who display elevated symptoms of internalizing and/or externalizing problems, but who have not been formally diagnosed or who are not currently undergoing examination in outpatient clinics for a potential diagnosis. The children and/or their caretakers are referred to or seek help from municipal level frontline services. The study is conducted in 24 Norwegian municipalities that vary in size and demography, and together represent all health regions in Norway. All participating municipalities are part of a municipal implementation network hosted by Norwegian Center for Child Behavioral Development (NUBU; Norwegian acronym), and thus have experience with implementation of EBIs in their services. The 24 data collection municipalities have signed a written agreement and committed to contribute with at least two practitioners to be trained in SPARCK, whom each will deliver four intervention cases during the data collection period. Additionally, all municipalities will provide one case to the UC condition for each case to the SPARCK condition. Both SPARCK practitioners and practitioners in the control condition work in municipal frontline services. SPARCK practitioners will not provide cases to the UC condition.

Participant recruitment will follow regular care procedures for screening and inclusion into frontline services. Practitioners will use their clinical judgments to infer whether participants display problems compatible with the target group in the study (see eligibility criteria). No formal standardized assessment procedures for inclusion in the project will be implemented. However, some municipalities have already implemented more formal regular practice procedures for screening and will continue to utilize these in this study. After the family has been identified as a possible case for the study, a practitioner will conduct a recruitment interview to inform about the study and to ensure that the family is eligible according to inclusion and exclusion criteria (see eligibility criteria below). Written informed consent will be obtained from eligible families before inclusion in the study, see Fig. 1.

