### Data collection

In this study we use a combination of web-based questionnaires to be completed by one parent on mobile phones, pen-and-pencil questionnaires to the children for those who are seven years or older, and hair samples from one parent (i.e., the parent who answers the questionnaires) and the child to measure biomarkers of stress (i.e., cortisol and DHEA). The families receive a hair-sample kit with instructions and necessary equipment for cutting the correct amount of hair. The pen-and-pencil questionnaires for the children is distributed together with the hair-sample kits.

Parent reported data (i.e., the web-based questionnaires by one parent) will be gathered at three time points; pre (T1), post (treatment termination, T2), and six months follow-up (six months after post, T3; see Fig. 1). If the UC group receives open-ended treatments or counselling is delayed in either condition, we will gather T2 parent reported data at 25 weeks after T1 (i.e., T2 is gathered 25 weeks after T1 at the latest). Hair samples will be gathered through participant self-sampling from one parent and the child in all families. Both the hair samples and the child report pen-and-pencil questionnaire is gathered in connection with T1 and at T2. They are instructed to send a text message to the NUBU study coordinators when they have posted the hair-samples and the child questionnaire in the mail, upon which they are ready to be randomized. At T2, the hair-sample kit and the child questionnaire are sent out approximately four weeks after the termination of the intervention (or two weeks after week 25). The delay in the data gathering of hair-samples is simply because the hair-samples reflect the retrospective average bio-marker levels across an 8-week period (two-centimeter hair segment samples).

Finally, register data from Statistics Norway for CWS service contacts and from the Norwegian Patient Register for service referrals will be collected. Data will be obtained two years after post-treatment. Parents have consented to collection of register-data up to 5 years after follow-up, but the potential five-year long-term register data collection depends on the project receiving additional funding.

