In both study conditions we digitally assess intervention content, practitioner characteristics, and service-related details as reported by practitioners. For practitioners in the UC condition 1, a practitioner report questionnaire (PRQ) has been developed to evaluate therapist background, service-related aspects, educational background, training in EBIs, and counselling experience etc. Moreover, PRQ at T2 evaluates whether an EBI were provided and what intervention components that were given to families in the condition 1 counselling. Parallel assessments are conducted for the condition 2 SPARCK practitioners on practitioner and service characteristics. Additionally, condition 1 practitioners supply information regarding intervention administered to condition 1 families, outlining if a standardized or EBI has been provided, intervention components, session frequency, dosage, recipients, and targeted issues. Condition 1 practitioners provide their background and service-related details at intervention onset, whereas intervention specifics are reported upon completion or by week 25. In contrast, condition 2 practitioners complete a web-based fidelity questionnaire (FidQ) designed and optimized during the SPARCK development phases, detailing recipients, intervention strategies employed, pedagogical tools used, client engagement, and parental assessment of Goals in intervention. This SPARCK questionnaire is completed weekly after each session. Condition 2 practitioners report service and practitioner characteristics at project start-up. Parent and practitioner reported working alliance will be assessed using the 12-item Working Alliance Inventory – short form (WAI-S; [70]). Parent reported satisfaction with intervention will be reported with a User satisfaction questionnaire (UserSQ) adapted from the Family satisfaction survey [71]. UserSQ contains 5-items assessed on 5-point Likert scales ranging between “Not correct” and “Correct all the time”. Finally, register outcomes on child referrals to mental health outpatient specialized services and CWS services (RBD) will be collected two years after T3 follow-up assessments.

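### The register outcome for H7 is given two conflicting dates tied to the end of treatment, and its child welfare component can count contact that existed before, or formed part of, trial care

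*Protocol article*

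**What the plan says.** **Outcome.** H7 (Aims and research questions) counts as unfavourable a referral to BUP or any instance in which children "have contact with the Child Welfare Services (CWS) in the following two years compared to children in the UC condition". No start date is attached.

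**Timing.** Two sentences date the register data:
- Data collection: "Data will be obtained two years after post-treatment".
- Measures: the register outcomes "will be collected two years after T3 follow-up assessments".

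Data collection places T3 six months after T2. T2 is the end of treatment, and its assessment takes place no later than 25 weeks after T1.

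**Setting.** The abstract places the trial in the "frontline services of child welfare, health, school health and school psychological counselling services in 24 Norwegian municipalities". The Aims section says that "frontline municipal service sectors, such as child welfare, health, school health and school psychological counselling services, are responsible for providing targeted preventive interventions". On recruitment: "The children and/or their caretakers are referred to or seek help from municipal level frontline services". On delivery: "Both SPARCK practitioners and practitioners in the control condition work in municipal frontline services".

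**Eligibility.** Children referred to or treated in BUP for internalizing or externalizing problems are excluded. Contact with CWS as such is not an exclusion.

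**Treatment length.** SPARCK has at most 12 sessions, planned weekly, though longer intervals are allowed. UC has no upper limit on sessions or weeks.

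**The concern.** There are two separate problems.

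First, the two timing statements cannot both be right, and H7 does not settle which applies. Both also hang on a date after randomisation that depends on how long treatment lasted. A comparison of how many children had an event needs the same observation time from the same origin in both arms. An origin or end date that moves with treatment length does not guarantee that.

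Second, the two parts of H7 are treated differently at entry. Because prior BUP referral for the target problems is excluded, a later BUP referral is largely a new event. Nothing comparable applies to CWS, although some families may reach the trial through child welfare or be treated there. Where such contact is in the register, it is scored as a failure of prevention. That dilutes a true effect. It could also create a false one if trial-related contact lasts longer in one arm.

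**Working it through.** The plan states no event rate, effect size or power for H7, so there is no figure to reproduce. The check compares the timing statements and then shows, under stated assumptions, how the problems act.

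**1. The two dates**
- Data collection: T2 + 24 months.
- Measures: T3 + 24 = (T2 + 6) + 24 = T2 + 30 months.
- Difference: 6 months. If counting started at T2, the second period would be 30/24 = 1.25 times the first.

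**2. Dependence on treatment length**

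Suppose that events are counted from entry to T2 + 24 months (104 weeks), that SPARCK ends at 12 weeks and that UC reaches the 25-week limit. For simplicity, measure from T1.
- SPARCK: 12 + 104 = 116 weeks.
- UC: 25 + 104 = 129 weeks, so 129/116 = 1.11 times as long.
- With a constant event rate, no true effect and an assumed 25% risk over 116 weeks, the UC risk is 1 − 0.75^(129/116) = 27.4%. That is 2.4 points in favour of SPARCK from follow-up length alone.
- With equal treatment length in both arms the difference is zero. The documents do not say where between or beyond these cases the trial will lie.

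If counting instead starts at T2 or T3, lengths can be equal, but referrals between randomisation and that date are not counted.

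**3. Dilution by contact common to both arms**

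Let s be the share of families in each arm who are registered with CWS whatever the intervention does, and let p_U and p_S be the true risks of a new event. The observed risks are s + (1 − s)p_U and s + (1 − s)p_S, so the observed difference is (1 − s)(p_U − p_S).

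The values of s, p_U and p_S are assumptions. The 126 per arm is the planned 252 divided by 2, with no allowance for dropout or clustering.

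| s | 30% vs 15%: difference | Power | 30% vs 20%: difference | Power |
|---|---|---|---|---|
| 0 | 15.0 points | 82% | 10.0 points | 45% |
| 0.1 | 13.5 | 65% | 9.0 | 33% |
| 0.2 | 12.0 | 50% | 8.0 | 25% |
| 0.3 | 10.5 | 39% | 7.0 | 20% |
| 0.5 | 7.5 | 23% | 5.0 | 13% |

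**4. Possible bias from open-ended UC**

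Let p = 25% be the true risk in both arms (no effect) and s the share treated in CWS. Let that contact run on into the counting period in a fraction u of these UC families and v of these SPARCK families. The spurious difference is (1 − p) × s × (u − v).
- s = 0.3, u = 0.4, v = 0.1: UC 0.25 + 0.75 × 0.3 × 0.4 = 34.0%; SPARCK 0.25 + 0.75 × 0.3 × 0.1 = 27.25%; difference 6.75 points.
- s = 0.1, u = 0.3, v = 0.2: 0.75 points.
- s = 0.4, u = 0.4, v = 0.1: 9.0 points.

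All of these inputs are assumed. If u = v there is no bias, only dilution.

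**The case against.** **The two sentences state when data are retrieved, not when counting starts.** This is correct. Retrieval at either date could cover everything since randomisation, so a reader who infers that early referrals will be lost goes beyond the text. But these are the only timing statements for this outcome. They conflict, and H7 does not supply the missing origin.

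**The CWS event is not shown to be met by design.** A reader might infer that every family served by child welfare automatically has the H7 event. The documents do not support that. Child welfare is one of four service types listed, the share of families recruited or treated there is not given, and nothing says whether trial care there is recorded as a contact in the Statistics Norway register. The problem holds only to the extent that such contact is registered.

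**Randomisation balances prior contact.** It does in expectation, since allocation is by pairs within municipality after pre-assessment. Prior contact is therefore mainly a source of dilution, not bias. Bias needs contact that differs between arms after randomisation. Open-ended UC makes that possible but does not establish it. The exclusions for abuse and for other concurrent systematic interventions also remove some CWS cases, but not CWS contact in general.

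**The 25-week limit and flexible SPARCK spacing narrow the gap in T2.** They do, and step 2 is an illustration, not an estimate. The limit applies to the assessment, however; the article does not say that UC itself stops then.

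**Event definitions belong in the analysis plan.** Much detail does, and H7 does not rule out analysing the two components separately. The conflicting dates and a hypothesis that scores any CWS contact as unfavourable are nonetheless in the printed text.

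**Conclusion.** The point holds in this form. The timing of the H7 register outcome contradicts itself by six months, and H7 names no start. Both dates depend on T2, so counting from randomisation to either one can give unequal follow-up, while counting from T2 or T3 omits earlier events. Separately, H7 treats any CWS contact as unfavourable in a trial run partly in child welfare services, with no exclusion for prior CWS contact.

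Only the six months comes from the documents. The dilution factor (1 − s) is exact when s is the same in both arms, but s is unknown. Every event rate, power value and spurious difference above rests on assumed inputs. The documents do not support the claim that the event is guaranteed for child welfare families, that early referrals are certainly lost, or that the comparison is certainly biased.

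The point should be corrected, but it concerns one secondary hypothesis. H1 and the sample size are not affected.

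**What to change.** 1. **One window.** Define a single fixed-length period starting at the randomisation date, the same for every family, and bring H7, Data collection and Measures into line with it. Retrieve the data once the last family has completed it.
2. **Separate components.** Analyse BUP referral and CWS contact separately.
3. **New CWS contact.** Make the main CWS analysis new contact among children with no CWS contact before randomisation, or keep all children and adjust for prior contact.
4. **Trial-related contact.** Where the register allows, exclude contact that is only delivery of SPARCK or UC. Where it does not, add a sensitivity analysis that starts counting in both arms at one fixed time after randomisation, later than the 25-week limit. This reduces the problem but does not remove it if UC runs on longer.

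**Cost.** Wording changes in three places and a register request that includes prior CWS contact, if consent covers it; the article mentions consent for later data but does not say whether earlier data are included. Restricting to children without prior contact gives a smaller denominator for the CWS component. Register retrieval lies years ahead, so no data collection already under way has to change.

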## Methods

### Study design

This study is a two-armed parallel group randomized controlled effectiveness superiority trial with assessment of key variables at pre-, post-, and six-months follow-up. Participants (i.e., parents) will be allocated either to receive SPARCK or UC.

### Participants, recruitment, and randomization

The target group in this study is caretakers of children between 4 and 12 years who display elevated symptoms of internalizing and/or externalizing problems, but who have not been formally diagnosed or who are not currently undergoing examination in outpatient clinics for a potential diagnosis. The children and/or their caretakers are referred to or seek help from municipal level frontline services. The study is conducted in 24 Norwegian municipalities that vary in size and demography, and together represent all health regions in Norway. All participating municipalities are part of a municipal implementation network hosted by Norwegian Center for Child Behavioral Development (NUBU; Norwegian acronym), and thus have experience with implementation of EBIs in their services. The 24 data collection municipalities have signed a written agreement and committed to contribute with at least two practitioners to be trained in SPARCK, whom each will deliver four intervention cases during the data collection period. Additionally, all municipalities will provide one case to the UC condition for each case to the SPARCK condition. Both SPARCK practitioners and practitioners in the control condition work in municipal frontline services. SPARCK practitioners will not provide cases to the UC condition.

Participant recruitment will follow regular care procedures for screening and inclusion into frontline services. Practitioners will use their clinical judgments to infer whether participants display problems compatible with the target group in the study (see eligibility criteria). No formal standardized assessment procedures for inclusion in the project will be implemented. However, some municipalities have already implemented more formal regular practice procedures for screening and will continue to utilize these in this study. After the family has been identified as a possible case for the study, a practitioner will conduct a recruitment interview to inform about the study and to ensure that the family is eligible according to inclusion and exclusion criteria (see eligibility criteria below). Written informed consent will be obtained from eligible families before inclusion in the study, see Fig. 1.

**Fig. 1 Fig1:**
[figure not shown]
Flow of participants in the study

Randomization will be performed using an online database hosted by the external provider, Klinforsk, at the Norwegian University of Science and Technology [59] www.klinforsk.no. Accordingly, the allocation sequence will be blinded for researchers, study personnel and practitioners working in the municipalities. Stratified pairwise randomization will be used, meaning that pairs of children/familieswill be recruited from each municipality after which one child/family will be randomized to receive SPARCK and the other to UC. If a second case is not recruited within a four-week period, a single case block randomization backup solution will be used to prevent prolonged delays for the first recruited child/family. In case of such single case randomization, the block size will be blinded for researchers, study personnel and practitioners in the municipalities, to prevent bias in the recruitment process. Participants will be randomized after signing a written informed consent and completing the pre-assessment.

While blinding is difficult or even unfeasible in human-delivered interventions like SPARCK and in the UC condition interventions, efforts have been made to mask participants from knowing which study condition they belong to. All information materials use neutral language such as "condition 1" (UC) and "condition 2" (SPARCK), and municipal recruitment personnel are trained not to provide any biased information to participants. However, it may be challenging to maintain masking during and after receiving the intervention, and participants may figure out which study condition they belong to if practitioners reveal the study condition.

